### Health economics

We aim to estimate the short-term cost-effectiveness of the case-finding intervention from the NHS perspective. The research team will use a proforma to record the number of practices who accept the educational presentation on HCV, including the number of practice staff attending and job titles. Practice staff will be provided with a proforma to record the time taken to extract and screen the lists of high-risk patients and to exclude ineligible patients each time the Audit + search is run. The proforma will also ask practice staff to record the number of letters sent out to patients inviting them to book an appointment. At both intervention and control sites practice staff will extract information from the electronic patient record on the consultations, laboratory tests, radiology and prescriptions received by patients during the study period identified as high-risk by Audit +. This dataset will be de-identified and assigned a unique study ID by a data analyst at PHE laboratories, as described above.

This will allow us to identify HCV case-finding consultations (in the intervention practices) and opportunistic HCV testing consultations (in intervention and control practices). We will also use the linked dataset to identify post-diagnosis resource use (e.g. follow-up consultations with GPs and specialists, prescriptions). Where available, national unit costs [17, 18], or locally estimated unit costs if unavailable, will be used to value the time spent inviting patients to case-finding appointments and delivering HCV-related care to high-risk and untreated patients throughout the study period. We will calculate the incremental cost per new diagnosis of HCV and the incremental cost per new patient initiating HCV treatment in intervention versus control practices. Uncertainty will be explored using cost-effectiveness acceptability curves, which estimate the probability of intervention cost-effectiveness for various willingness-to-pay thresholds [19].

Provided that the intervention improves case-finding and treatment, we will extrapolate short-term costs and outcomes of the intervention using a health economic model that is parameterised to the UK health provider perspective including liver disease progression stages and QALYs used in previous exercises for NICE and the Human Tissue Authority (HTA) [7, 20–22]. The model also can be dynamic, incorporating the potential prevention benefit of diagnosing and treating people who inject drugs as well as people who have ceased injecting or other patient groups. Costs and health benefits are discounted at 3.5 % per year in the base case according to NICE guidelines. Results will be expressed in terms of incremental cost-effectiveness ratios (ICERs), calculated by dividing the difference in costs between the intervention and usual care strategies, divided by the difference in health outcomes, in this case QALYs. For each economic analysis, multivariate uncertainty analyses and numerous one-way sensitivity analyses will be undertaken so that the robustness of the model results can be examined; and we will also plot cost-effectiveness acceptability curves.

### Qualitative interviews

Health care professionals (HCPs) and patients’ views and experiences of the intervention will be examined through the conduct of semi-structured qualitative interviews. The qualitative findings will assist in highlighting the perceived effectiveness and acceptability of targeted HCV case-finding and increasing HCP and patient awareness within primary care.

#### Qualitative study design

Qualitative telephone interviews will be conducted with primary care patients and the interviews will consider and compare (1) views and experiences of being approached opportunistically at the practice or contacted by letter and invited for a consultation with their GP, (2) the acceptability of being approached for a HCV test, (3) views on whether any additional interventions may be helpful, and (4) (if tested HCV-positive) views and experiences of referral to secondary care and on-going assessment/treatment.

HCPs involved at the intervention practices will also be interviewed to gather data on (1) their views and experiences, (2) changes in clinical practice, (3) acceptability and feasibility of the intervention, (4) information and support needs, and (5) their attitudes to the future implementation of the intervention within primary care.

#### Interview participant sampling and recruitment

Patients offered a HCV test at participating intervention practices will be asked if they are willing to be contacted about taking part in a qualitative interview at the time of their consultation. From participants who indicate that they are willing to be contacted, a purposive sample will be drawn in relation to (1) primary care practice, and (2) socio-demographic variables (e.g. gender, age and ethnicity). Telephone interviews will be conducted with a sample of patients who (1) declined a HCV test, (2) accepted a HCV test, (3) tested positive for HCV and were subsequently referred to secondary care. HCP (including general practitioners and nurses) involved in implementing the intervention will be purposively sampled in relation to (1) primary care practice, (2) professional role, and (3) length of time since qualification/seniority.

Those sampled will be contacted by the researcher and asked if they are interested in taking part in an interview. Patients will be interviewed either after they have been offered a HCV test or for patients who have already tested positive for HCV before the study, a sample of these will be interviewed following their first attendance for assessment and/or treatment. The sample sizes will be determined by the need to achieve data saturation, such that no new themes are emerging from the data by the end of data collection [23]. This is likely to include up to 15 HCPs and 15 patients at participating intervention practices.

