### Sample size

We based our initial sample size calculation on an average practice of 6500; with 4225 adults aged 15–65, we would expect approximately 1 % (42) of people to have an injecting history and in Bristol approximately 40 % (17) of those to have chronic HCV [13]. As a minimum we assume that 10 high-risk patients, based on the algorithm and markers of previous injecting history, will be identified and that the intervention increases uptake of HCV testing from 5 to 17 % of those high-risk patients. Then we require a sample size of 46 practices (23 intervention and 23 control, 230 high-risk patients identified in each arm) to achieve 90 % power at the 5 % significance level. We have assumed an intra-cluster correlation coefficient (ICC) of 0.05, and hence a design effect of 1.45, to accommodate variation in testing rates across practices.

This is a conservative sample size calculation to ensure a large enough number of practices and sufficient power to measure the main intervention effect on uptake of HCV case-finding and diagnosis as well as referral and assessment for treatment. First, practices being approached for the study and identified by the CRN have an average practice list size of 10,000 and, therefore, approximately 6500 adults aged 15–65. Second, it is likely that 2 % of adults will have an injecting history – combining estimates of people currently on opioid substitution treatment and ex-injecting drug users [14, 15]. Third, early pilot studies suggest that it is likely that 80 or more people for an average practice will be identified by the algorithm. This gives approximately 1840 people per arm and substantial power to detect a difference in uptake of HCV testing. In addition, if we assume that two thirds of people diagnosed with chronic HCV attend hepatology for assessment then the case-finding rates of 5 and 17 % convert to HCV treatment readiness rates of 1.3 and 4.4 % and 72 % power (with an ICC of 0.05) to detect a true difference in HCV treatment readiness. As we will adjust the statistical analysis for testing rate and whether a practice is within or outside the Bristol area, this will accommodate some of the clustering, and so it is likely that we will have sufficient power to detect a difference in HCV treatment assessment as well as HCV testing uptake.

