The practice manager will be asked to install the Audit + software onto the practices’ clinical system. Practice staff training will include details on how to install and use the Audit + software as part of the intervention. Within the Audit + software, the HCV audit will be used to identify potentially eligible patients who have pre-defined Read codes defining them as ‘high-risk’ (see Appendix). The Audit + software identifies all patients with one or more of the codes. Patients excluded are those: tested recently for HCV; who have been referred to hepatology; receiving palliative care; who have raised ALT and tested for HCV. The audit will be run and updated every 24 hours on the GP system. GPs will be asked to screen the resultant list at the beginning of the intervention and then regularly, at intervals defined by the practice, to identify new patients during the remainder of the study period. GPs will be permitted to exclude any patient identified by the audit where they feel that an invitation for HCV testing or discussion of treatment is not appropriate. Eligible patients’ records identified by the audit will be automatically flagged by the software to encourage opportunistic testing if the patient attends the surgery. Practice staff can manually switch off the flagging should they feel that the patient is not eligible for a HCV test, if the patient declines a test or if the patient accepts the offer of a test, by entering a specific set of Read codes. Practice staff administrators will also be asked to send out a letter to each patient identified by the audit informing them that the practice is taking part in a study and that they may contact patients by telephone, e-mail or text (whichever is preferred by the practice) to book an appointment to discuss having a test. The patient invitation letters will be automatically processed using the integrated mail-merge facilities built within the software. Diagnosed patients are managed as usual/in standard care at the practice.

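### Patients are asked about interviews only at a consultation, so letter recipients with no consultation at which a test was offered cannot be sampled on the acceptability of letter recall

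*Protocol article*

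**What the plan says.** All references are to the Protocol article.

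- **Aim.** Qualitative study design lists, as the first topic to be considered and compared, "views and experiences of being approached opportunistically at the practice or contacted by letter and invited for a consultation with their GP". The second topic is the acceptability of being approached for a test.
- **Letter recall.** In the section on identifying patients with risk markers, practice administrators are asked to "send out a letter to each patient identified by the audit informing them that the practice is taking part in a study". Telephone, e-mail or text may follow, to book an appointment. The same section has the software flag eligible records, so that a test can be offered when the patient comes in for any reason.
- **Route into the interviews.** Under Interview participant sampling and recruitment, patients offered a test "will be asked if they are willing to be contacted about taking part in a qualitative interview at the time of their consultation". Then: "From participants who indicate that they are willing to be contacted, a purposive sample will be drawn".
- **Groups.** Interviews are planned with patients who "1) declined a HCV test, (2) accepted a HCV test, (3) tested positive for HCV and were subsequently referred to secondary care". Of patients already known to be positive before the study, "a sample of these will be interviewed following their first attendance for assessment and/or treatment".
- **Size.** Up to about 15 patients, governed by data saturation.
- **Eligibility.** Participant eligibility asks for registration at an intervention practice, the offer of a test, age 18 or over, ability to consent and a telephone. It does not ask for attendance.

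**The concern.** The two approach routes are not sampled on equal terms. Everyone approached opportunistically is already in contact with the practice and can be asked about an interview on the spot. On the letter side, only those who later reach a consultation can be asked. Not responding is the obvious way for a recall letter to fail, and a patient for whom it failed in that way, with no later consultation, has no route into the sample.

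What is at stake is how far the patient interviews can answer their own first two questions. If people who stay away find the letter unwelcome, alarming or irrelevant, their reasons will not be heard, and patients' accounts of the letter may look more favourable than the full range of views. The article gives some reason to expect a difference: its Background notes that people who injected long ago may not disclose this to their GP, and that a hidden infected population deserves attention in later search strategies. The Discussion looks to roll-out elsewhere in the UK, where the reasons for non-response would matter in practice.

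**Working it through.** The point rests on the recruitment wording and not on a stated figure, so the main check is to follow each kind of intervention-practice patient through that wording.

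| Patient sent the letter | Has a consultation at which a test is offered? | Can be asked about an interview? |
|---|---|---|
| Books, accepts the test | Yes | Yes |
| Books, declines the test | Yes | Yes (declined group) |
| Ignores the letter, later comes for another reason, flag prompts an offer | Yes | Yes |
| Ignores the letter and all follow-up, no such consultation | No | No |
| Refuses when contacted to book, no such consultation | No | No |

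The declined group does not close the gap. Its members are also asked at a consultation, so it captures refusal of a test once the matter is discussed, not failure to respond to the letter. Patients positive before the study are interviewed after a first attendance, so they have attended too. The saturation rule does not help, because saturation can be reached among attenders alone. The iterative steps under Interview conduct and Qualitative data analysis change the topic guide, not the recruitment route.

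The restriction comes from the recruitment route and not clearly from eligibility, which turns on having been offered a test. Whether a letter inviting someone to discuss testing counts as an offer is not stated.

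**Scale.** Inputs from Sample size: 23 intervention practices; 10 high-risk patients per practice as a minimum, or 80 from the pilot work; and the assumption that "the intervention increases uptake of HCV testing from 5 to 17 % of those high-risk patients".

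- Identified per arm: 23 × 10 = 230, or 23 × 80 = 1,840. Both agree with the article.
- Untested in the intervention arm: 230 × (1 − 0.17) = 190.9, about 191; or 1,840 × (1 − 0.17) = 1,527.2, about 1,527.

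These are ceilings. The untested include patients who attended and declined, and patients whom the GP judged unsuitable to invite. Let f be the share of the untested who got the letter and had no consultation at which a test was offered. The documents do not give f, so it is left as an assumption:

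| f (assumed) | Unreached, of 1,840 | Share of identified patients |
|---|---|---|
| 0.25 | 1,527.2 × 0.25 ≈ 382 | 21% |
| 0.50 | 1,527.2 × 0.50 ≈ 764 | 42% |
| 0.75 | 1,527.2 × 0.75 ≈ 1,145 | 62% |
| 1.00 | 1,527 | 83% (ceiling) |

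The table shows only how the answer moves with f. No row is an estimate.

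**The case against.** Several points against this are sound.

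- **Not everyone whom the letter failed is lost.** A reader might infer that all patients for whom the letter did not work are excluded by design. The documents do not support that. The record flag means that someone who ignored the letter and later attended can be offered a test and asked about an interview, and such a patient can speak to both routes. Nor does the text say that a consultation must be face to face, so a telephone consultation could count. The gap is confined to people with no consultation at which a test was offered.
- **Patients' views are not the only evidence on acceptability.** A reader might infer that acceptability will be judged by attenders alone. Health care professionals are also interviewed on acceptability and feasibility, uptake of testing is the primary outcome, and letters sent are recorded for the economic evaluation. Poor response to recall would therefore be visible. That evidence bears only indirectly on why people stayed away.
- **Population coverage is a poor yardstick for a purposive sample.** About 15 interviews claim no representativeness, and a percentage reached does not measure their quality. This stands. The argument rests on a relevant type of patient being unreachable, not on how many there are.
- **The eligibility wording may itself exclude non-attenders.** If the letter is only an invitation to discuss a test, a non-attender has not yet been offered one. This is a fair reading, and the remedy has to deal with it.
- **A reply slip reaches only those who reply.** True: people who respond to nothing remain unreached. The slip, together with a question at the follow-up contact, would still admit those who do not want an appointment but are willing to talk.

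**Conclusion.** The point holds in a limited form. As written, the recruitment route cannot sample patients who received the recall letter and had no consultation at which a test was offered. Patients' accounts of the letter route, for the first two interview topics, will come only from those who booked or who attended for another reason and were flagged. Professional interviews and recorded uptake give only indirect evidence about the rest.

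The size of that group cannot be derived from the article. The figure of 83%, about 1,527 of 1,840, is an upper bound that takes the planned 17% uptake and 80 identified patients per practice as given; it should not be read as an expected number.

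The consequence stays within the nested qualitative study. Nothing here touches the primary outcome or the power. It is a cheap improvement worth making, not a flaw in the trial.

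**What to change.** 1. Add an interview reply option (a slip or a telephone number) to the mail-merged letter, open to people who do not want an appointment, and have practices ask the same question at the follow-up telephone, e-mail or text contact.
2. Add a purposive group of patients invited by letter who did not attend, alongside those who declined, accepted, or tested positive and were referred, within the planned sample of up to 15 patients.
3. Clarify in Participant eligibility that, for the interviews, being invited by letter counts as being offered a test.
4. State in advance that, if few or none of this group reply, conclusions on the acceptability of letter recall will be limited explicitly to patients who had a consultation.

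The cost is a small change to the letter and the interview procedures, with what should be a minor amendment. The planned number of interviews need not rise. The reply rate will probably be low, and spreading about 15 patients over four groups in place of three leaves each slightly thinner. Practices were still being recruited when the article was submitted, so the change could have been made at that stage.

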#### Interview conduct

All interviews will be conducted by telephone. Participants will be asked to provide their verbal informed consent to take part immediately before the interview. A flexible topic guide will be used in order to assist questioning during in-depth individual interviews. Topic guides will be modified as necessary throughout the course of the study to reflect findings as they emerge. With informed consent from participants, interviews will be audio-recorded using a digital voice recorder, transcribed and anonymised to protect confidentiality.

#### Qualitative data analysis

Interview transcripts will be checked for accuracy and then imported into NVivo10 qualitative data analysis software to aid management and analysis of data. Analysis will begin shortly after data collection starts and will be ongoing and iterative. Analysis will inform further data collection: for instance, analytic insights from data gathered in earlier interviews will help identify any changes that need to be made to the topic guide during later interviews. Thematic analysis [24], utilising a data-driven inductive approach will be used to scrutinise the data in order to identify and analyse patterns and themes of particular salience for participants and across the dataset.

## Discussion

This trial has the potential to make an important impact on patient care and will provide high-quality evidence to help general practitioners make important decisions on HCV testing and onward referral. The intervention is scalable and, therefore, if found to be effective and cost-effective can be readily rolled out and implemented elsewhere in the UK in response to new NICE recommendations on improving HCV case-finding.

## Trial status

At the time of manuscript submission, this trial was still in the practice recruitment phase.

## Abbreviations

ALT, alanine aminotransferase; CRN, Clinical Research Network; GP, general practitioner; HCP, health care professional; HCV, hepatitis C virus; HTA, Human Tissue Authority; ICC, intra-cluster correlation; ICER, incremental cost-effectiveness ratio; NHS, National Health Service; NICE, National Institute for Health and Care Excellence; NIHR, National Institute for Health Research; NRES, National Research Ethics Service; PCR, polymerase chain reaction; PHE, Public Health England; PWID, people who inject drugs; QALY, quality-adjusted life year; RCGP, Royal College of General Practitioners; RNA, ribonucleic acid

## Appendix

### HCV audit

A HCV test algorithm was developed and piloted at two local general practices before its integration into the Audit + software (BMJ Informatica). The HCV test algorithm was designed to identify registered patients with high-risk HCV markers or patients previously diagnosed who failed to initiate or complete treatment. The search terms included (1) age 18–75 years old, (2) previous intravenous drug use (IDU) history, (3) opiate prescription (including methadone or buprenorphine), (4) opiate misuse, (5) blood transfusion prior to 1991, (6) blood products prior to 1996, (7) transplant prior to 1992, (8) infection with HIV, (9) infection with hepatitis B virus (HBV), (10) born to a mother with HCV, (11) child in care, (12) prison history, (13) altered ALT levels, (14) patients tested for HCV over 1 year previous, before the intervention. Identified individuals considered by GPs to be unsuitable for a discussion about HCV testing or treatment were excluded. Patients also automatically excluded by the HCV audit included (1) patients referred to hepatology, (2) patients tested less than 1 year prior to the intervention, (3) patients receiving end of life/palliative care, and patients with raised ALT levels who have been tested for HCV.

The list of codes are available from the authors and given in Additional file 1. Spirit Checklist also available in Additional file 2.
